#### Post-operative activity profile

Descriptive statistics will be used to analyse post-operative activity.

#### Factors associated with post-operative walking time

Bivariate analysis will be used to examine the association between the total time spent walking, and pre-operative mobility, function and physical activity, post-operative back, leg and wound pain, post-operative complications and the need for supervision while walking.

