## Method

### Aims

This research will investigate the relationship between the time spent walking in the week following lumbar surgery, and recovery of physical function. The primary aim is to establish whether the amount of walking patients do in the week following lumbar spinal surgery predicts improvement in function at six months. The data collected will also be used to generate an activity profile to describe the overall patterns of activity in the first post-operative week, and to identify factors that may influence the amount of activity patients undertake.

The research questions are:Does the amount of time spent walking during the week after lumbar spinal surgery predict improvement in function at six months?What proportion of time do patients spend performing active tasks (standing and walking) compared to sedentary behaviour (sitting and lying) in the week following lumbar spinal surgery?Is the amount of time spent walking in the first post-operative week influenced by restricted pre or post operative physical function, post-operative pain or complications, or the need for supervision while walking?

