### Outcome measures

An outcome assessment timeline and summary of assessment tools used is provided in Table 1.

**Table 1 Tab1:** Timeline of outcome assessment

Pre-operative (baseline)	
Baseline demographics:	Age, sex, smoking status, height, weight, diabetic history
History of back/leg symptoms:	Duration of symptoms, neurological deficit
Physical function:	ODQ, SF-36
Pain:	Back and leg pain (NRPS)
Physical activity:	IPAQ-SF
Psychological status:	Depression (PHQ-9), anxiety (GAD-7)
Post-operative (days 1–7):	
Surgical procedure:	Decompression, discectomy, fusion; single or multi-level
Accelerometry:	Time spent walking, step count, time spent in sedentary and active postures, number of walks
Pain:	Back, leg and wound pain (NRPS)
Supervised walking:	Patient/physiotherapist reported
Post-operative complications:	Complications requiring medical intervention and/or limit walking time
Post-operative (6 months):	
Physical function:	ODQ, SF-36
Patient satisfaction:	5 point likert scale
Post-operative complications:	Complications requiring medical intervention

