#### Independent (confounding) variables

Data will be collected for variables where there is either evidence to suggest they influence outcome following lumbar spinal surgery, or there is or strong theoretical rational for their inclusion. This will include age, gender, current smoking status [14, 15], obesity [14, 18], diabetes [14, 16, 17], depression [19, 20], duration of pain/symptoms [35], neurological deficit [14], anxiety, pre-operative activity, pre-operative mobility, surgical procedure, multi-level surgery, and pre-operative function.

Depression will be assessed using the Patient Health Questionnaire Depression Scale (PHQ-9), using a cut off score of ≥10 [36]. The PHQ-9 is a short, valid and reliable measure of depression, and has been recommended for use within the chronic back pain population [37]. Anxiety will be scored using the Generalised Anxiety Disorder 7-item Scale (GAD-7), using a cut off score of ≥10 [38]. The GAD-7 is a brief, seven question scale used to screen for, and assess the severity of anxiety. It has been validated in the general population [38]. Neurological deficit will be assessed by asking the participant if he/she is aware of any changes to the sensation or strength in their affected lower limb. This level of information is deemed appropriate for this study, as any sensory or motor deficit that the participant is unaware of is unlikely to have an impact on functional ability. Pre-operative activity will be assessed using the International Physical Activity Questionnaire Short Form (IPAQ-SF) [39, 40]. The IPAQ-SF is a brief, reliable seven item questionnaire that requires participants to report on physical activity undertaken over the previous seven day period [39, 40]. Physical activity is categorised into low, moderate and high activity levels. As it is expected that the majority of participants will report either low or moderate activity levels, the two categories of low and moderate/high activity levels will be used for data analysis. Baseline ODQ score will be used as a measure of pre-operative function. Pre-operative mobility will be categorised based on the response to Section 4 (Walking) on the ODQ. Participants will be categorised as having limited mobility if they score 3 or more - unable to walk more than 500 m, require a walking aid, or are confined to bed.

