#### Relationship between time spent walking and outcome

Multivariable logistic regression analysis will be used to investigate the relationship between the time spent walking in the first week after surgery and outcome at six months using SPSS software. The dependent variable in the logistic regression model will be the change in score on the ODQ, SF-36 (PCS), NRPS (back) and NRPS (leg) between baseline and six months. The change in scores on the ODQ, SF-36 (PCS) and NRPS will be dichotomised based on the threshold required to demonstrate a substantial clinical benefit.

Thresholds required to meet the minimum clinically important difference (MCID) have been identified for the ODQ, the SF-36 (PCS) and the NPRS [41] (Table 2). In addition, thresholds required to obtain a substantial clinical benefit (SCB), where patients report a major improvement in symptoms, have been defined for the ODQ, SF-36 (PCS) and NRPS in the lumbar fusion population [42] (Table 2). For the purpose of this study it has been assumed that SCB following lumbar fusion surgery provides a fair estimate of substantial clinical benefit following lumbar surgery in general. These thresholds allow the change in scores to be categorised as minimal improvement (below MCID threshold), moderate improvement (above MCID threshold, below SCB threshold) and substantial improvement (SCB threshold or greater).

**Table 2 Tab2:** MCID and SCB thresholds

Outcome measurement tool	MCID (points change)	SCB (points change)
ODQ	10	18.8
SF-36 (PCS)	4.9	6.2
NPRS (back)	2	2.5
NRPS (leg)	2	2.5

As all participants in this study are undergoing surgery with the aim of improving pain and physical function, it expected that the majority of participants in this study will report an improvement in scores above the MCID threshold. Therefore the SCB threshold will be used to analyse the impact of walking time on outcome (minimal/moderate improvement compared to substantial improvement). For each of the four dependent variables a multivariable logistic regression model will be generated comparing participant outcome relative to the SCB threshold.

With the exception of pre-operative function and surgical procedure, all confounding variables will be dichotomised (Table 3).

**Table 3 Tab3:** List of independent variables and classification for statistical analysis

	Classification				
1. Post-operative activity	Time spent walking (minutes)				
2. Age	1. < 65 years	2. ≥ 65 years			
3. Gender	1. Male	2. Female			

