## Discussion

The findings from this research will assist physiotherapists to identify patients who are expected to have either very good or poor post-operative outcomes based on their activity levels immediately following surgery, and inform physiotherapists about whether increasing activity should be a focus of post-operative rehabilitation. This will help to guide patient management during the inpatient phase, by identifying patients who are at risk of poorer outcome due to limited walking time. These patients may benefit from ongoing rehabilitation and outpatient physiotherapy services. This information will also provide a foundation for further research into interventions designed to optimise post-operative activity such as patient education resources, improved monitoring and management of post-operative pain, or the provision of additional physiotherapy sessions for patients who require supervision while walking.

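### Research question 3 asks what influences walking time, but its only stated analysis is unadjusted bivariate testing, which cannot separate a factor's contribution from that of age or extent of surgery

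*Protocol article*

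**What the plan says.** The Aims section of the protocol article lists three research questions. The third begins "Is the amount of time spent walking in the first post-operative week influenced by restricted pre or post operative physical function" and goes on to post-operative pain, complications and the need for supervision. The lead-in to the questions states the same intent: "to identify factors that may influence the amount of activity patients undertake".

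The analysis for this question is one sentence, in the last subsection of Data analysis, which deals with correlates of walking after the operation. The method is stated as follows: "Bivariate analysis will be used to examine the association between the total time spent walking". On the other side of that association, the sentence lists "pre-operative mobility, function and physical activity, post-operative back, leg and wound pain, post-operative complications and the need for supervision while walking". That makes eight factors: three pre-operative, three pain sites, complications and supervision.

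Adjustment appears only for question 1, whose outcome is assessed at six months: "Multivariable logistic regression analysis will be used to investigate the relationship between the time spent walking in the first week after surgery and outcome at" that time point. The multicollinearity check is described for those models too. Surgery type is recorded in Table 1 as "Decompression, discectomy, fusion; single or multi-level". Age, surgical procedure and multi-level surgery are listed as confounding variables and classified in Table 3.

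The Discussion says the study will be a foundation for research into interventions. Its examples include management of post-operative pain and "the provision of additional physiotherapy sessions for patients who require supervision while walking".

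**The concern.** The question is worded as influence, and the method delivers unadjusted association. The cohort mixes decompression, disc surgery and fusion, at one or several levels. A larger operation could plausibly bring more pain, more complications, more supervision and less walking together. A bivariate difference in walking time between supervised and unsupervised patients would then partly reflect the operation, and the planned tests could not show how much.

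Two further features make the separate results hard to read:

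- Pre-operative function is the baseline ODQ score, while "Pre-operative mobility will be categorised based on the response to Section 4 (Walking) on the ODQ". These two factors overlap by construction.
- Complications, as defined in the section on factors associated with walking immediately after surgery, include events recorded because they limited activity. That factor is partly defined by the outcome.

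What is at stake is the reading of a secondary question whose factors match the Discussion's examples for further research. The primary analysis is not affected.

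**Working it through.** **The plan's own figure.** The document gives no sample size, power or significance level for question 3. Its stated minimum of 150 belongs to the question 1 logistic model: 5 events × 15 variables = 75 events, and 75 / 0.5 = 150. The 50% outcome share is not stated; it is the value needed to reach 150. This figure reproduces but does not bear on question 3.

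**Use of covariates, side by side.**

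| | Question 1 | Question 3 |
|---|---|---|
| Outcome | Six-month change, dichotomised | Total walking time, continuous |
| Method | Multivariable logistic regression | Bivariate only |
| Age, procedure, levels | Listed as confounders | Not mentioned |
| Collinearity check | Stated | Not mentioned |

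**How large could confounding be?** All inputs here are assumptions, because the document gives none. Let a share f of patients have fusion, let fusion lower walking by d SD, and let a binary factor have prevalence p1 in fusion and p0 in other patients, with no effect of its own. The expected unadjusted difference is

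d × [P(fusion | factor) − P(fusion | no factor)].

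*One worked case:* f = 0.35, p1 = 0.60, p0 = 0.20, d = 0.8, n = 200.

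- P(factor) = 0.35 × 0.60 + 0.65 × 0.20 = 0.21 + 0.13 = 0.34.
- P(fusion | factor) = 0.21 / 0.34 = 0.618.
- P(fusion | no factor) = 0.14 / 0.66 = 0.212.
- Spurious difference = 0.8 × (0.618 − 0.212) = 0.32 SD.
- With 68 against 132 patients, the standard error is about 0.16 SD, so the two-sided 5% test rejects in about 53% of samples.

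*Simulation over a range:* f = 0.30, 3,000 runs per cell, two-sided 0.05, n = 250. The entries are unadjusted false-positive rates.

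| Factor prevalence, other vs fusion | d = 0 | d = 0.3 | d = 0.5 | d = 0.8 |
|---|---|---|---|---|
| 30% vs 30% | 5.3% | 4.6% | 4.7% | 4.8% |
| 30% vs 45% | 5.3% | 5.8% | 7.5% | 13.2% |
| 30% vs 60% | 5.5% | 9.6% | 16.3% | 33.2% |
| 20% vs 70% | 5.1% | 17.3% | 40.7% | 75.2% |

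The first row (factor unrelated to surgery type) and the first column (surgery type unrelated to walking) stay near 5%. Where both links exist the range is about 6% to 75%. At n = 150 the same cells run from 5.3% to 51.8%. With surgery type added to a linear model, the rate at n = 250 is 4.4% to 5.5% in every cell with d above zero.

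**Parameters needed for an adjusted model** (intercept not counted).

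- Step 1: activity 1, age 1, procedure 2, levels 1, one ODQ measure 1 = 6. Step 2 adds three pain sites, supervision and complications = 5. Total 11.
- With both mobility (1) and the five ODQ bands of Table 3 (4), step 1 becomes 1 + 1 + 2 + 1 + 1 + 4 = 10, and the total is 15.
- Patients per parameter: from 200 / 15 = 13 to 250 / 11 = 23. The plan projects about 250 patients; 200 is an assumed number left for analysis.

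**The case against.** The analysis subsection speaks of association, in its heading and its text, and bivariate tests do deliver unadjusted association. The question is secondary to one named primary aim. The Discussion offers examples for further research; it does not select a treatment target. An unadjusted association can also be useful for recognising patients who walk little, whatever the cause. All of this stands and limits the weight of the point. It does not close the gap, because the question in the Aims is still worded as influence and no other analysis is offered for it.

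A reader might infer more: that supervision, pain and complications will look influential merely because they track the type of surgery. The document does not support that. It contains no data linking surgery type to any of these factors or to walking time, both links are needed, and the factors may have real effects. A reader might also add a family-wise error figure computed as if the eight tests were independent. The factors are not independent, as the two ODQ measures show, so such a figure would not apply.

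Adjustment has limits too. It cannot remove the circularity in complications that were counted because they limited activity, and an adjusted estimate in an observational cohort still does not establish influence.

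**Conclusion.** The point holds as a mismatch between a stated question and a stated method. It is not a detail left to an analysis plan, since the article names the method. Unadjusted bivariate tests cannot separate a factor's contribution from that of age, procedure or number of levels, although the plan collects all three and treats them as confounders elsewhere.

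Confounding by extent of surgery is a plausible risk of unknown size. Under the assumed inputs, the false-positive rate for a factor with no effect runs from about 5%, if either link is absent, to well above 50% at the projected sample size if both are strong. Those percentages rest on assumed fusion shares, prevalences and effect sizes, and on a two-group simplification of surgery type. They show what could happen and do not predict this study's result.

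**What to change.** Keep the bivariate results as description. Add a multivariable linear regression of total walking time, transformed if skewed, in two steps:

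1. Pre-operative activity, age, surgical procedure, multi-level surgery, and either ODQ Section 4 mobility or the ODQ score as a continuous variable. Do not enter both ODQ measures unless collinearity has been checked.
2. Add first-week pain, supervision and complications. Include a sensitivity analysis that leaves out complications counted only because they limited activity.

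Report the results as adjusted associations, and reword research question 3 from influence to association.

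No new data are needed. The cost is a little more analysis and about 11 to 15 parameters on roughly 200 to 250 patients. The step 2 factors may partly mediate those in step 1, so pre-operative factors should be read from step 1, and their step 2 coefficients should not be taken as total associations.

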## Discussion

The findings from this research will assist physiotherapists to identify patients who are expected to have either very good or poor post-operative outcomes based on their activity levels immediately following surgery, and inform physiotherapists about whether increasing activity should be a focus of post-operative rehabilitation. This will help to guide patient management during the inpatient phase, by identifying patients who are at risk of poorer outcome due to limited walking time. These patients may benefit from ongoing rehabilitation and outpatient physiotherapy services. This information will also provide a foundation for further research into interventions designed to optimise post-operative activity such as patient education resources, improved monitoring and management of post-operative pain, or the provision of additional physiotherapy sessions for patients who require supervision while walking.

## Abbreviations

EVP: Events per predictor variable
GAD-7: Generalised Anxiety Disorder 7-item Scale
IPAQ-SF: International Physical Activity Questionnaire Short Form
MCID: Minimum clinically important difference In addition
NPRS: Numeric pain rating scale
ODQ: Oswestry Disability Questionnaire
PHQ-9: Patient Health Questionnaire Depression Scale
SCB: Substantial clinical benefit
SF-36 (PCS): SF-36 physical component summary
SVPHF: St Vincent’s Private Hospital, Fitzroy
